Currently, unidimensional frailty assessment remains predominant in research involving people living with HIV or AIDS, while research on multidimensional frailty status is still insufficient, and the factors leading to multidimensional frailty in hospitalized older adults living with HIV or AIDS are not yet clear. Therefore, we will explore multidimensional frailty as the main outcome. The theory of unpleasant symptoms (TOUS), as a mid-level theory, is commonly used to establish methodological methods and analyze results, or as a theoretical framework for analyzing influencing factors [13,14]. The theory suggests that factors that affect symptoms can be divided into 3 parts: physiological, psychological, and environmental. The three interact and influence each other, jointly affecting disease symptoms and influencing the outcome of symptoms. Guided by TOUS, we categorized potential frailty factors in hospitalized older adults living with HIV or AIDS into physiological, psychological, and environmental domains based on literature review and clinical practice. Ultimately, all included potential influencing factors were identified and finalized through online expert consultation.

Early-stage frailty in older adults living with HIV or AIDS is often relatively insidious. However, to our knowledge, there is relatively little research and development in China on frailty prediction tools for hospitalized population. To address these gaps, we aim to develop and validate a prediction model using 3 machine learning algorithms. By comparing their performance, we seek to enhance risk prediction accuracy, ultimately improving patient prognosis and health outcomes.

This prospective observational study aims to (1) determine the prevalence of multidimensional frailty among hospitalized people living with HIV or AIDS aged ≥50 years, (2) identify factors associated with frailty guided by the TOUS, and (3) develop and validate risk prediction models.

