### Sample Size

Frailty occurrence in people living with HIV or AIDS represents a binary outcome. Previous studies reported a frailty incidence of 59.3% in hospitalized older adults living with HIV or AIDS, which was assessed using the FRIDE frailty scale [16]. Due to the current lack of a frailty prediction model for HIV/AIDS patients, it is not possible to determine *R*^2^ through previous models. Based on the proportion of outcome events, the maximum *R*^2^ (*R*^2^ cs_max) is calculated to be 0.7416. Assuming that the new model can explain 20% of the variability, the expected *R*^2^ is 0.1483 (=0.7416×20%). We expect the predictive model to include 5 to 10 predictor variables, based on “pmsampsize(type=‘b’, csrsquared=0.1483, parameters=10 , prevalence=0.593).” In this formula, csrsquared represents the ability of the expected prediction model to explain outcome variability; parameters represent the total number of candidate variables expected to be included; and prevalence refers to the prevalence of frailty events in older people living with HIV or AIDS in China based on previous research. The calculation indicates that a minimum sample size of 556 is required. A total of 330 events were expected, corresponding to 33 events per predictor variable. The above results are calculated using the pmsampsize package in R Statistical Software (version 4.4.0) [17].

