### Definition of Outcomes

At present, the frailty assessment methods adopted in various domestic studies are inconsistent, and there are significant differences in research results. Most studies use a single physiological dimension frailty scale (such as frailty phenotype). We believe that frailty phenotype, as a universal frailty assessment tool including core indicators such as weight loss and perceived fatigue, may be affected by HIV-specific factors. For example, a decline in immune system function leads to the occurrence of opportunistic infections, as well as nausea, vomiting, diarrhea, and nutrient absorption disorders caused by the side effects of most antiviral drugs, which makes people living with HIV or AIDS more prone to weight loss. In addition, most antiretroviral drugs cause patients to experience fatigue and exhaustion, which may exacerbate physical inactivity. Current research on multidimensional frailty is expanding. Global studies have confirmed the strong applicability of the Tilburg Frailty Indicator in people living with HIV or AIDS [18,19]. Its comprehensive advantage in assessing frailty across physical, psychological, and social domains may render it more suitable for the objectives of this study than unidimensional tools.

The main outcome of this study is the presence of frailty among people living with HIV or AIDS. We use the Tilburg Frailty Indicator for reporting, developed by Gobbens et al [20] and localized by Li et al [21]. The scale consists of 15 items, with physiological dimensions including 8 items: physical health, natural weight loss, walking difficulties, balance, vision, hearing, grip strength, and fatigue; the psychological dimension includes 4 items: memory, depression, anxiety, and coping ability; and the social dimension includes 3 items: living alone, social relationships, and social support. If the patient’s current condition meets the description of 5 or more items, it indicates that the patient has frailty. The final assessment results of the scale will be confirmed by 2 specialists in infection and immunology.

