### Statistical Analysis

SPSS software (version 26.0; IBM Corp) and R Statistical Software (version 4.4.0; R Foundation for Statistical Computing) are used for data analysis. Categorical variables are presented as frequencies and percentages. Normally distributed continuous data are expressed as mean (SD), while nonnormally distributed continuous or ordinal variables are summarized as median (IQR). Group comparisons employed *t* test or one-way ANOVA for normally distributed continuous variables, Mann-Whitney *U* test (2 groups) or Kruskal-Wallis *H* (multiple groups) test for non-normal/ordinal data, and chi-square test for categorical variables. For baseline data, a *P* value <.05 is considered statistically significant, indicating a significant difference in baseline characteristics between the group with frailty and the group without frailty. For missing data, considering the instability of missing values, this study used multiple imputation method (imputation tool: “mice” package in R Statistical Software [version 4.4.0]) to fill in the missing parts. Participants will be excluded if there are 3 or more candidate variables missing. After imputation, sensitivity analysis will be used to validate the plausibility of the Missing at Random assumption and the robustness of the imputation results. By comparing the results of multiple imputation datasets with complete case analysis (ie, removing missing data), we further validate the robustness of our main conclusions.

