### Model Development and Validation

The sample size of this study is relatively small. This study uses logistic regression (LR) as the benchmark for performance comparison. LR has certain advantages in handling limited sample sizes and can demonstrate feature coefficients and significance levels. Although random forest (RF) has the risk of overfitting in small sample situations, it has certain advantages in handling complex nonlinear relationships. We will minimize the risk by adjusting decision tree parameters and cross-validation. Support vector machine (SVM) is particularly suitable for handling situations with high feature dimensions but relatively small sample sizes, and its regularization properties help control the risk of overfitting. As one of the tree ensemble algorithms, XGBoost also has the risk of overfitting and relatively complex parameter tuning. Neural networks have high requirements for sample size and poor clinical interpretability for small sample studies. We hope to ensure the robustness of the model to a large extent in this small sample study. For future larger-scale research, more complex machine learning methods will be used.

Randomly split the training set and validation set in a 7:3 ratio, and use the following machine learning algorithms for modeling: LR model, RF, and SVM. Univariate analysis combined with least absolute shrinkage and selection operator regression will be used to screen predictive factors. To address nonlinearity, we will analyze the relationships between relevant factors and HIV frailty risk using restricted cubic splines and incorporate them as spline terms in the model. Restricted cubic splines can also indirectly capture potential interactions between features. Interactions and complex nonlinear decision boundaries will be handled by selecting nonlinear kernel functions in SVM. The primary model performance evaluation metric is accuracy, which represents the proportion of correctly predicted samples in classification tasks. This will be considered alongside precision, recall, *F*_1_-score, and area under the receiver operating characteristic curve for comprehensive assessment. Through integrated comparison, the algorithm achieving optimal balance across these metrics will be selected as the final model for predicting frailty status in people with HIV.

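### The search for factors associated with frailty (Objective 2) uses the 15-item Tilburg count only as frail versus not frail, although the full 0-15 score is collected and only prevalence and classification need the cut

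*Protocol article*

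**What the plan says.** The Introduction of the protocol article lists three aims: prevalence of multidimensional frailty, a search for factors ("identify factors associated with frailty guided by the TOUS"), and prediction models.

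Definition of Outcomes describes the Tilburg Frailty Indicator: "The scale consists of 15 items", across physical, psychological and social domains. The range 0-15 is not printed but follows from the count. The section then sets the threshold: "If the patient’s current condition meets the description of 5 or more items, it indicates that the patient has frailty".

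Later steps keep the two-class form:
- Sample Size: "Frailty occurrence in people living with HIV or AIDS represents a binary outcome".
- Statistical Analysis: a P value below .05 is read as "indicating a significant difference in baseline characteristics between the group with frailty and the group without frailty".
- Model Development and Validation: factors are screened by univariate analysis and LASSO for logistic regression, random forest and support vector machine models of frailty status.

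That last section also says: "The sample size of this study is relatively small". It gives this as a reason for limiting the choice of algorithms.

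**The concern.** A cut at 5 treats patients with 4 and 5 items as opposites and patients with 5 and 15 items as identical. A classifier or a prevalence estimate must accept this. A search for associated factors need not, because the total is already in the dataset. The article argues for the Tilburg scale over the frailty phenotype, but gives no reason for using only the cut in the association analysis.

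At stake is the yield of Objective 2. Factors of weak-to-moderate strength are the ones most likely to be missed, and estimated associations will be less precise than the collected data allow. In a study that limits its methods because it regards its sample as small, this is an avoidable loss.

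**Working it through.** **1. The plan's own figure.** Inputs from Sample Size: Cox-Snell R² 0.1483, 10 parameters, prevalence 0.593. With a target shrinkage of 0.9 (assumed; not printed):

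n = P / [(S − 1)·ln(1 − R²/S)] = 10 / [(−0.1)·ln(1 − 0.1483/0.9)] = 10 / (0.1 × 0.18006) = 555.4, rounded up to 556.

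The other two criteria give about 244 and 371, so this one governs. Events: 556 × 0.593 = 329.7, about 330, or 33 per parameter. Maximum R² computes to 0.7411 against the stated 0.7416, which leaves 556 unchanged. The stated size reproduces. It was set for a binary prediction model, not for power per factor.

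**2. Information lost by the cut.** The 0.593 comes from another frailty scale (Sample Size), so applying it to Tilburg ≥5 is an assumption.

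- *Common-odds model.* Ratio of full-score to binary information = (1 − Σpⱼ³) / [3p(1 − p)], where pⱼ is the share of patients at each score. The denominator is 3 × 0.593 × 0.407 = 0.724. For a beta-binomial score on 0-15 with 59.3% at or above 5, Σpⱼ³ is about 0.01, so the ratio is 0.99/0.724 ≈ 1.37 (1.36 to 1.37 over plausible spreads). Share lost: 1 − 1/1.37 ≈ 27%.
- *Normal score.* Efficiency of a cut = φ(z)²/[p(1 − p)], with z = 0.235 and φ(z) = 0.388. This gives 0.1506/0.2414 = 0.624, a loss of about 38%. Splits from 30% to 70% give 0.58 to 0.64, so the borrowed prevalence matters little.

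**3. Power per factor from the plan's R².** Assumptions: 10 independent predictors of equal strength and a two-sided 5% test for each. Total likelihood-ratio chi-square = −n·ln(1 − 0.1483), and one tenth of it is each predictor's noncentrality. The full score multiplies this by 1.35, slightly below the ratio in step 2. The sizes are 70% of 556 (389), the stated development set (445) and the whole (556).

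| n | Noncentrality, binary | Power, binary | Power, full score | Difference (points) |
|---|---|---|---|---|
| 389 | 62.4/10 = 6.24 | 70.5% | 82.7% | 12.2 |
| 445 | 71.4/10 = 7.14 | 76.2% | 87.4% | 11.2 |
| 556 | 89.2/10 = 8.92 | 84.8% | 93.5% | 8.7 |

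Simulations calibrated to the same R² and prevalence, with linear regression on the score, gave at n=389, 445 and 556:
- one common factor behind all items: 73% vs 92%, 79% vs 94%, 87% vs 98%
- predictors acting only on their own domain: 69% vs 86%, 72% vs 88%, 79% vs 92%

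A small separate run that fitted the proportional-odds model itself gave the same power as linear regression: 89% for both against 75% binary at n=389, and 97% for both against 86% at n=556.

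**4. Power without the plan's R².** A beta-binomial score and a binary factor present in 30% or 50% of patients, n from 389 to 556:

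| Power, full score | Power, cut at ≥5 | Loss (points) |
|---|---|---|
| 60% | 42-44% | 17-18 |
| 70% | 50-52% | 18-20 |
| 80% | 60-62% | 18-20 |
| 90% | 73-75% | 15-17 |
| 95% | 82-83% | 12-13 |

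A simulated rounded score with a continuous factor at n=556 lost about 19 points at correlation 0.10, 13-14 at 0.15, about 6 at 0.18 and about 3 at 0.20. At n=389 the losses at 0.18 and 0.20 were about 14 and 9.

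**The case against.** The strongest reply is that the article defines its main outcome as presence of frailty, with a cut taken from the published instrument. Objective 2 asks about factors associated with that condition. A score model asks something else: what shifts the item count at any level. This stands in part. It is a reason to keep the binary model and not to demote it, but not a reason to leave the count unused.

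Second, factor search and classifier share one pipeline, sized for a binary model, and the article sets no power target per factor. This also stands: no planned power is missed. Nor do ten equal, independent predictors tested at 5% describe 31 candidates, some plainly correlated, that pass through LASSO.

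Third, Statistical Analysis lists ANOVA and Kruskal-Wallis for multiple groups, which a two-class outcome would not require and which might hint at score comparisons. That list is generic. It names no analysis of the Tilburg total, and the only comparison it spells out is "a significant difference in baseline characteristics between the group with frailty and the group without frailty".

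Fourth, Tilburg items on anxiety, depression, memory, weight loss and social support overlap with candidate scales, so some added power would go to associations built in by shared content. That is a fair caution, and it applies to the binary outcome too.

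Two stronger readings are tempting. A reader might infer that the cut costs every factor a fixed 10 to 18 points; the calculations range from about 3 to 20 depending on effect size, score distribution and n. A reader might also infer that enrolment cannot help; in step 3 the gap narrows from 12.2 to 8.7 points between n=389 and n=556, and Results reports 603 enrolled.

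**Conclusion.** The point holds as a missed opportunity in the analysis of Objective 2, not as an error in the outcome definition or the sample size. As described, the article uses only the ≥5 cut when it looks for associated factors, and this discards about 27% of the outcome information under common odds, or about 38% for a normal score. The resulting loss of power per factor is about 3 to 20 points. It peaks at 18 to 20 where the score analysis would have 70-80% power, and falls to 3 to 6 for the stronger factors (correlations of 0.18 to 0.20) at n=556.

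The direction is secure and the size depends on assumptions. The article gives no effect size, score spread or power for a single factor, and its 59.3% comes from a different scale. A reader might infer that 556 is too small or that the binary outcome should become a sensitivity analysis. The documents support neither: 556 reproduces for its stated purpose, and the cut is the defined main outcome.

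**What to change.** Keep Tilburg ≥5 as the main outcome for prevalence, class labels and the prediction models. For Objective 2, prespecify a proportional-odds (or linear) regression on the 0-15 total score and report it alongside the binary logistic model. Check the common-odds assumption by comparing the proportional-odds estimates with the binary fit at the ≥5 cut, and state what will be reported if they differ.

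The cost is some analysis wording and a few lines of R. No new data or patients are needed, and Results states that no data analysis has been conducted, so the addition can still be prespecified. The downsides are small. The score model describes a shift in item count rather than crossing the cut, and the proportional-odds version assumes one odds ratio across levels. Associations with candidate scales that share content with Tilburg items need a cautionary note under either model.

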### Prediction Variables

#### Determination of Candidate Variables

The selection of predictive variables for this prediction model is based on a review of literature and consensus opinions by an expert group, taking into account its practicality in clinical settings. Possible clinically relevant variables will be selected as candidate predictors of frailty and evaluated after the patient’s admission examination is completed. Through 3 group discussions and 1 online expert consultation meeting, a total of 31 candidate predictor variables were identified and classified into physiological, psychological, and environmental factors based on TOUS. The variables to be explored are detailed in the following subsections.

#### Physiological Factors

The sociodemographic data assessed included age, gender, marital status, place of residence, education level, work situation, average monthly income, medical payment method, height, weight, BMI, smoking history, alcohol consumption history, and exercise status [22-25].

Disease-related conditions include time of HIV diagnosis, start time of antiviral treatment, route of infection, and the types of diseases that have been diagnosed at present and other associated complications (heart failure, hypertension, cerebrovascular disease, diabetes, moderate or severe liver disease, moderate or severe kidney disease, chronic obstructive pulmonary disease, and tumors) [26-29].

The Pittsburgh Sleep Quality Index (PSQI) developed by Buysse is used for collecting sleep data [30,31]. It includes 7 dimensions: sleep quality, bedtime, sleep duration, sleep efficiency, sleep disorders, hypnotic drugs, and daytime dysfunction, totaling 18 items. Each dimension is scored from 0 to 3 points, with 0 indicating the absence of sleep disorders, 1 indicating mild disorders, 2 indicating moderate disorders, and 3 indicating the presence of severe disorders. The total score ranges from 0 to 21, with a PSQI >7 indicating sleep problems.

Nutritional status is assessed using the Mini Nutritional Assessment-Short Form scale developed by Rubenstein and consists of 6 items, including changes in appetite, weight, mobility, activity, mental health status, and BMI index [32,33]. The total score is 0 to 14 points, with <8 points indicating malnutrition, 8 to 11 points indicating a risk of malnutrition, and ≥12 points indicating good nutritional status. Research has shown that this scale has good sensitivity and specificity in China [34].

Neurocognitive function is evaluated using the International HIV Dementia Scale, a rapid screening tool developed by Sacktor et al [35,36,37]. It can screen for psychomotor speed, attention, working memory, executive function, and language. Including 3 tests with a total score of 12, patients with a score of ≤10 should be further evaluated for possible dementia. Studies have shown that the International HIV Dementia Scale has better efficiency in detecting the neurocognitive performance of patients using antiretroviral drugs [38].

#### Psychological Factors

The Hospital Anxiety and Depression Scale is used for anxiety and depression [39,40]. Mainly used for screening anxiety and depression status of patients in hospitals. The Hospital Anxiety and Depression Scale is divided into 7 anxiety items and 7 depression items. Each item is scored from 0 to 3 points, with higher scores indicating more severe anxiety and depression. This scale has good reliability and validity in the application of people living with HIV or AIDS in China [41,42].

#### Social Factors

The Chinese version of the Social Support Rating Scale developed by Xiao [43] is used to measure an individual’s social support status, including three dimensions: objective support, subjective support, and personal utilization of social support [44,45]. There are a total of 10 items, with a total score of 12 to 66 points. The higher the score, the higher the level of social support. A general total score of ≥45 indicates a high level of support, 23 to 44 indicates a moderate level of support, and ≤22 indicates a low level of support. Social Support Rating Scale is widely used in people living with HIV or AIDS [46].

Laboratory examination indicators were HIV load, CD^4^ T lymphocyte count, albumin, C-reactive protein (CRP), interleukin-6 (IL-6), and soluble tumor necrosis factor receptors (sTNFR1 and sTNFR2) [47-50]. It is worth noting that although inflammatory indicators such as IL-6 and sTNFR1/2 are potential predictive factors for hospitalized older adults living with HIV or AIDS, these items do not have clinical applicability due to their noninfectious and immunological routine clinical testing content, and relevant test results cannot be obtained.

### Data Acquisition

Data will be acquired through questionnaires and hospital medical record systems. We use face-to-face, on-site distribution, and questionnaire collection to obtain general patient information (demographic and sociological information, lifestyle habits, and disease-related conditions), frailty scores, PSQI, anxiety and depression scores, nutrition scores, and social support scores. Physiological measurements will be taken on-site. For participants with lower educational levels or who are unable to complete the survey independently, researchers will fill in the questionnaire on their behalf based on their answers and verify them one by one. To ensure that the natural heterogeneity of the population is not disturbed by human factors, the questionnaire collection process will strictly follow the pre-established standard operating procedures.

The relevant laboratory tests will be conducted within 24 to 48 hours after admission. The collection of venous blood samples is strictly carried out by specialized nurses in the field of infection and immunology, following standard operating procedures. This step is included in the routine admission examination, and we do not charge any additional examination fees for it. We will inform patients before conducting the study that we need to use some personal biochemical test data and enter it into the dataset after obtaining consent. Obtain laboratory test indicators, including HIV load, CD^4+^ T lymphocyte count, albumin, and CRP, through the test records in the case record system of Changsha First Hospital. However, this study did not collect inflammatory indicators such as IL-6 and sTNFR1/2, which may affect the in-depth analysis of the mechanism of frailty inflammation. It is recommended to prioritize supplementary verification in future research.

Neurocognitive function assessments will be administered face-to-face by 2 researchers within 48 to 72 hours of admission. The examination is conducted in a separate interview room to avoid different patients in the same ward being informed of the test content in advance, which may affect the results of the neurocognitive function examination.

